**Purpose**

The primary objective is to evaluate the efficacy of advanced periodontal self-care in patients with early stage periodontal diseases on endothelial function.

**Background**

A remarkable association between periodontal disease and atherosclerotic cardiovascular disease (ACVD) has been reported, although their causative relationship remains controversial.

**Study Rationale**

Entry of oral bacteria, including periodontal pathogens and/or their products into the bloodstream, is common regardless of periodontal status. The immune response following persistent bacteremia from periodontal lesions may lead to ACVD. Identification of periodontal care effectiveness against ACVD require well-designed interventional studies.

Endothelial dysfunction occurs in the early stages of atherosclerosis and can be assessed by measuring flow-mediated dilatation (FMD) of the brachial artery. Therefore, FMD appears to be an appropriate surrogate marker to evaluate periodontal care effectiveness against ACVD.

**Goals of the Study**

1. To evaluate the efficacy of advanced periodontal self-care on endothelial function as measured by FMD and serum asymmetric dimethylarginine (ADMA; an endogenous NO synthase inhibitor) level compared to the control group.

2. To evaluate the association between FMD and serum ADMA level.

**Duration of the Study**

The study is estimated to complete enrollment within 6 months from study initiation. The duration of this study for each subject will be a maximum of two and a half years.

**Advanced Periodontal Self-care:**

Advanced periodontal self-care involves application of disinfectant with a custom-fabricated prescription tray to the teeth surface and periodontal pockets in addition to standard periodontal care.

**Product Intended Use**

Advanced periodontal self-care is to be used for a removal of periodontal and cariogenic pathogen from oral cavity.

**Product Acquisition**

The disinfectant and tray will be purchased by Department of Translational Research, Tsurumi University School of Dental Medicine from Medoc International Co. Ltd. and Shiken Corp., respectively at no cost to the patient.

**Potential Risks and Benefits to Patients**

Every effort will be taken to prevent medical accidents. There are no potential risks to patients due to a patient being treated with standard care and/or advanced periodontal self-care.

Because each subject will be received standard of care for periodontal diseases, improvement of periodontal health condition will be expected. Improvement of endothelial function will also be expected if our theory is correct.

**Methods**

*Study Design*.

The study will be designed as a parallel group (1:1), 3-month follow-up, open-label, randomized controlled trial.

One control group of 55 subjects will undergo a typical standard care for periodontal diseases. The other test group of 55 will undergo an application of hypochlorous acid water with a custom-fabricated prescription tray in addition to standard care.

*Study Population and Selection Criteria*.

All aspects of the study and consent forms will be Institutional Review Board (IRB) approved prior to implementation.

All participants will require full informed consent, be willing and able to comply with all study requirements and will meet the following criteria;

- Male or female aged 18-70
- 20 or more functioning teeth
- Periodontitis with bleeding on probing (more than two sites) and/or with 4 mm or larger periodontal pocket depth (more than one site)

Subjects will be excluded from the study based on the following criteria;

- Difficulty in traveling alone to the institution
- Necessity for prosthodontic treatment
- Presence of an untreated carious cavity
- Having used systemic antibiotics within the previous 3 months
- Used regular medication for any other chronic disease
- Any other treatment in higher-priority than periodontal treatment
- Involvement with any other ongoing studies

*Recruitment methods*.

Subjects will be recruited from advertisements in social networking services, Tsurumi University Dental Hospital in Yokohama City, Ariyoshi Dental Clinic in Tokyo, and Kioicho Plaza Clinic in Tokyo.

*Data collection and reporting*.

Data will be collected at the baseline and 3 months after intervention at Tsurumi University Dental Hospital, Ariyoshi Dental Clinic or Kioicho Plaza Clinic. Data from the study will be maintained in Department of Translational Research, Tsurumi University School of Dental Medicine for 5 years after the date the investigation is published.

*Expected outcomes*.

Both standard care for periodontal diseases and advanced periodontal care will show improved patient outcomes on periodontal diseases.

It is the expectation that application of disinfectant to periodontal tissue with a custom-fabricated prescription tray will show improved patient outcomes on endothelial function (FMD and serum ADMA level) over standard care for periodontal diseases.

*Adverse reactions*.

There is no expectation of any adverse outcomes or reactions due to a patient being treated with standard care and/or advanced periodontal self-care.

All participants will be given access to contact info of the principal investigator or co-investigators. Any adverse reactions should be reported immediately to the principal investigator or co-investigators.

**Reasons for Withdrawal or Termination**

A subject may be discontinued from the study at any time if the subject or the investigators feels that it is not in the subject’s best interest to continue. The following is a list of possible reasons for study treatment discontinuation:

- Screening Failure
- Subject withdrawal of consent
- Subject is not compliant with study procedures
- Adverse Event that in the opinion of the Investigator would be in the best interest of the subject to discontinue study participation
- Protocol violation requiring discontinuation
- Lost to follow-up
- Contract diseases that make it difficult to continue research
- Subject death

All subjects are free to withdraw from participation at any time, for any reason, specified or unspecified, and without prejudice. Reasonable attempts will be made by the Investigator to provide a reason for subject withdrawals. The reason for the subject’s withdrawal from the study will be specified in the subject’s source documents and the Case Report Form. If a subject is withdrawn from treatment due to an adverse event), the subject will be followed and treated by the Investigator until the abnormal parameter or symptom has resolved or stabilized. The Investigator must make every effort to contact subjects who are lost to follow-up.

**Handling of Participant Withdrawals of Termination**

Although subjects may withdraw from the study at any time and for any reason, (or may be withdrawn at the Investigator’s discretion), subject withdrawal should be avoided as much as reasonably possible. In any case, appropriate follow-up for endpoints should be continued. Subjects who prematurely discontinue are not to be replaced. For subjects considered lost to follow-up, the Case Report Form must be completed up to the last visit performed.

**Premature Termination or Suspension of Study**

This study may be temporarily suspended or prematurely terminated if there is sufficient reasonable cause. Written notification, documenting the reason for study suspension or termination, will be provided by the suspending or terminating party to the investigators and the IRB, as appropriate. If the study is prematurely terminated or suspended, the principal investigator will promptly inform the IRB and will provide the reason(s) for the termination or suspension. Circumstances that may warrant termination or suspension include, but are not limited to:

- Determination of unexpected, significant, or unacceptable risk to participants
- Demonstration of efficacy that would warrant stopping
- Insufficient compliance to protocol requirements
- Data that are not sufficiently complete and/or evaluable
- Determination of futility

Study may resume once concerns about safety, protocol compliance and data quality are addressed and satisfy the IRB.

**Methods and Study Schedule**

Subjects eligible for the study will review and undergo informed consent. Once consented, subjects will be randomly assigned on a 1:1 basis to undergo:

- Control Group: Current standard care for periodontal diseases
- Test Group: Application of disinfectant with a custom-fabricated prescription tray in addition to standard care

*Visit for Screening (-60 to -1 days from Day 0)*

The following procedures will be performed at the Screening visit:

- Review the study with the subject and obtain written informed consent
- Assign the subject a unique screening/enrollment number
- Record demographics (age, gender)
- Review and record medical history, surgical history, and medication history to determine eligibility based on inclusion/exclusion criteria
- Document all current medications, including medications over-the-counter and herbal medications

*Visit for Treatment (Day 0)*

After baseline measurements, the following techniques will be used according to the arm the patient is randomized to:

Control Group:

The 55 subjects will undergo typical standard care for periodontal diseases.

Treatment Group:

The 55 subjects will undergo application of disinfectant with a custom-fabricated prescription tray in addition to standard care.

*Visit for endpoint measurements (Day 90)*

The following procedures will be performed at the visit for endpoint measurements:

- Assess for adverse events
- Document all current medications, including medications over-the-counter and herbal medications

*Unscheduled Visit*

The following procedures will be performed if the subject presents to the clinic at any other time point not specified above:

- Assess for adverse events
- Document all current medications, including medications over-the-counter and herbal medications

*Early Termination*

All subjects have the right to withdraw from study participation at any time during the study. If, for whatever reason, a subject withdraws from the study, an Early Termination visit will be performed.

The following procedures will be performed (if agreed upon by the subject) at the Early Termination visit:

- Assess for adverse events
- Document all current medications, including medications over-the-counter and herbal medications

**Randomization**

The eligible patients will be allocated randomly to the test or control group via the envelope method stratified by the smoking habit, which is a common risk factor for ACVD and periodontal diseases.

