| **Procedures** | Screening  Day -60 to -1 | Randomization  Baseline assessment  Day 0 (Control) | Baseline assessment  Day 0 (Test) | Final assessment  Day 90 ± 3 | Custom tray setting for control  (Optional) |
| Informed consent | X |  |  |  |  |
| Demographics | X |  |  |  |  |
| Dental history | X |  |  |  |  |
| Medical history | X |  |  |  |  |
| Concomitant medication review | X | X | X | X | X |
| Randomization | X |  |  |  |  |
| Dental examination ^a^ | X | X | X | X | X |
| FMD measurement |  | X | X | X |  |
| Serum chemistry ^b^ |  | X | X | X |  |
| Blood pressure measurement |  | X | X | X |  |
| Dentition impressions |  | X |  | X |  |
| Administer study intervention |  | X | X |  |  |
| Adverse event review and evaluation | X | X | X | X | X |
| ^a^ bleeding on probing, periodontal pocket depth; ^b^ ADMA, C-reactive protein | | | | | |

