**Conflicts of Interest**

[name] and [name] received research grant from Medoc International Co. Ltd; [name] received a research grant from Shiken Corp. There are no other declared potential conflicts of interest.

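### Allocation is fixed as envelopes in an open-label, three-clinic trial with no stated concealment safeguard, so the plan does not prevent recruiting staff from foreseeing or altering assignments

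*Protocol*

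**What the plan says.** The Randomization section describes allocation in one sentence: eligible patients are "allocated randomly to the test or control group via the envelope method stratified by the smoking habit". Smoking is the only stratification factor; clinic is not one.

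The Methods section (Study Design) states: "The study will be designed as a parallel group (1:1), 3-month follow-up, open-label, randomized controlled trial". Besides social-network advertisements, the recruitment sources are "Tsurumi University Dental Hospital in Yokohama City, Ariyoshi Dental Clinic in Tokyo, and Kioicho Plaza Clinic in Tokyo", and measurement takes place at the same sites: "Data will be collected at the baseline and 3 months after intervention at Tsurumi University Dental Hospital, Ariyoshi Dental Clinic or Kioicho Plaza Clinic".

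On sequence, Methods and Study Schedule says: "Once consented, subjects will be randomly assigned on a 1:1 basis to undergo" one of the two treatments. The Schedule of Activities is less clear. Its randomization row is marked at Visit 1 (screening, Day -60 to -1), while the heading of the Visit 2-1 column (Day 0) also names randomization.

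The protocol text at hand does not say how the envelopes are made, who prepares, holds or opens them, or whether blocks are used.

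**The concern.** Envelopes conceal allocation only as well as they are handled. If the person enrolling a patient can open an envelope early, read through it, take one out of order or set one aside, the arm can be matched to the patient. Because the trial is open-label, assignments become visible once treatment starts. If the sets are also balanced in blocks, part of the later sequence can be guessed.

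The primary comparison of FMD relies on the two arms being alike at entry. If patients who look likely to respond or comply go preferentially to the test arm, a difference arises without any treatment effect. The planned intention-to-treat analysis would keep the groups as assigned, but these would already differ. Covariate adjustment corrects only for what was measured, and staff may act on an impression that baseline FMD and smoking capture only in part.

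**Working it through.** **1. The protocol's own figure.** Sample Size Calculations gives a difference of 1%, SD 1.67%, two-sided α of 0.05, power 80% and N = 90.
- Normal approximation: n per arm = 2 × (1.960 + 0.842)² × 1.67² / 1² = 43.8, so 44 per arm and 88 in total.
- Two-sample t-test: 44.76, so 45 per arm and 90 in total.

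The figure reproduces with 1.67% read as the between-patient SD. The point does not rest on a sample-size error.

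**2. Safeguards sought in the protocol text.**

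| Safeguard | Found? |
|---|---|
| Opaque, sealed or sequentially numbered envelopes | No |
| Named holder separate from recruitment | No |
| Registration locked before the arm is known | No. Assignment follows consent and an enrolment number is given, but the number is not tied to envelope order |
| Central release of the arm | No |

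**3. How much could be guessed if blocks were used (not stated).** In a 1:1 permuted block of size 2k, someone who knows the block size and all earlier assignments in the block is certain of a share 1/(k + 1) of assignments on average. This gives 1/2 = 50% for blocks of 2, 1/3 = 33% for blocks of 4 and 1/4 = 25% for blocks of 6.

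**4. Illustration of the bias.** Only the SD and N come from the protocol. Two quantities are assumed: q, the share of allocations steered, and ρ, the correlation of the trait used for steering with the FMD outcome. The trait is taken as normal, and each steered patient is placed by its sign: above average to test, below to control. The mean absolute value of a standard normal is √(2/π) = 0.798.
- SE of the arm difference = 2 × 1.67 / √90 = 0.352
- Bias b = q × 2 × 0.798 × ρ × 1.67
- False-positive rate = Φ(−1.96 + b/SE) + Φ(−1.96 − b/SE)

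| q | ρ | b (FMD points) | b/SE | False-positive rate |
|---|---|---|---|---|
| 0 | – | 0 | 0 | 5.0% |
| 0.10 | 0.3 | 0.080 | 0.23 | 5.6% |
| 0.10 | 0.5 | 0.133 | 0.38 | 6.7% |
| 0.20 | 0.3 | 0.160 | 0.45 | 7.4% |
| 0.20 | 0.5 | 0.266 | 0.76 | 11.8% |

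With all 110 randomized patients analysed, SE = 2 × 1.67 / √110 = 0.318. The ranges become 5.7% to 7.0% for q = 0.10 and 7.9% to 13.3% for q = 0.20. A larger trial does not dilute this bias; the smaller SE makes a false-positive result more likely.

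**The case against.** The strongest reply is that the protocol is silent here rather than wrong. It does not say that recruiters keep the envelopes or that they are unsealed. The Protocol Summary names one study center, and stratifying by smoking alone fits a single set held there. Well-run envelopes can conceal allocation. Assignment follows consent, patients who discontinue are not replaced, and an intention-to-treat analysis is planned.

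Part of this stands. A reader might infer that recruiting staff hold the envelopes, or that steering will happen; the document supports neither. A reader might also infer that staff know every earlier assignment in a smoking stratum. That would need them to see the other clinics' assignments, or separate sets at each clinic, and neither is stated. The Conflicts of Interest section records that some individuals "received research grant from Medoc International Co. Ltd", a supplier of the trial, and that another had a grant from the tray supplier. Nothing shows that these people recruit or allocate, so the disclosure does not strengthen the point.

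The illustration is also generous in places. It assumes perfect sorting of every steered patient. If randomization takes place at Visit 1, staff would not yet have baseline FMD, which makes a correlation of 0.5 high.

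What does not stand is that the existing provisions offset the gap. Consent before assignment, an enrolment number, no replacement and intention-to-treat analysis do not stop an envelope being read, reordered or guessed. Nor is this a matter usually left to the SAP: concealment is trial conduct, and the protocol itself fixes the method.

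**Conclusion.** The point holds as an unprevented risk and should be corrected. The protocol chooses a mechanism whose protection depends wholly on handling rules, in an open-label trial at three clinics, and the text at hand gives no such rules. It does not establish that selection bias is present.

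The size is illustrative. Under the assumptions above, the spurious FMD difference is 0.08 to 0.13 points with 10% of allocations steered and 0.16 to 0.27 points with 20%, against a target of 1 point. The false-positive rates are about 6% to 7% and about 7% to 12% in place of 5%. The steered share and the correlation have no source in the document, and with less steering the inflation is smaller still.

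**What to change.** In the Randomization section, replace the envelopes with central release:
- An existing department member who takes no part in recruitment, treatment or FMD measurement holds a computer-generated list stratified by smoking, with block sizes not disclosed to the clinics.
- The clinic registers the consented, eligible patient by ID and smoking stratum.
- The entry is locked, and only then is the arm released.

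If envelopes are kept, the minimum is sequentially numbered, opaque, sealed envelopes for each smoking stratum, held by that same person with an opening log.

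The same amendment should reconcile the randomization visit in the Schedule of Activities, where the Visit 1 row entry and the Visit 2-1 column heading disagree.

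The cost is a protocol amendment, one call or e-mail per patient (110 in all) and a short wait at the visit. No extra patients or staff are needed, and the sample size is unchanged.

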**Sample Size Calculations**

The sample size was calculated based on a previous study that a sample size of 90 was needed to detect a 1% difference in FMD (primary outcome) between the two groups, with a standard deviation of the mean difference of 1.67% at a 2-sided α error of 0.05 and 80% power.

**Statistical Analysis Plan**

Primary Endpoint: FMD.

Secondary Endpoint: Serum ADMA level.

All analyses will be performed using per-protocol population as well as intention-to-treat population.

**Assessment of Safety**

Adverse events will be monitored and collected by the study team from the point of signed consent until the last day of study participation. For each adverse event, a detailed explanation will be obtained from the subject and subject’s medical record. All adverse event will be recorded on the Case Report Form.

*Definition of Adverse Event*.

An adverse event is defined as any unanticipated medical occurrence regardless to relationship of the investigative arm of the trial. An adverse event can be any unintended sign, lab abnormality, symptom, or disease associated with the trial. Any abnormality that presents during a medical test are to be defined as an adverse event if it produces clinical signs and/or symptoms, requires intervention, or deemed clinically significant by the Principal Investigator

**Data Handling and Record Keeping**

The collection of personal patient information will be limited to the amount necessary to achieve the aims of the research, so that no unneeded sensitive information is being collected.

Only study personnel will collect data. Hard copy documents will be retained for the duration of the study until data entry. All hard copy documents will be kept in a locked cabinet in the Department office. Data entry will be completed in the isolated secure persomal computer. Data will be exported into Excel file format (password protected), which will then be used for data analysis. Only de-identified data will be used for data analysis. All hard copy documents will be shredded within five years after publication.

**Institutional Review Board**

The protocol, informed consent form(s), and all participant materials will be submitted to the IRB for review and approval. Approval of both the protocol and the consent form must be obtained before any participant is enrolled. Any amendment to the protocol will require review and approval by the IRB before the changes are implemented to the study. All changes to the consent form will be IRB approved; a determination will be made regarding whether previously consented participants need to be re-consented.

**Protocol Deviation**

A protocol deviation is any noncompliance with the clinical trial protocol. The noncompliance may be either on the part of the participant, the investigators, or the study site staff. As a result of deviations, corrective actions are to be developed by the site and implemented promptly.

All protocol deviations/violations should be documented using the Protocol Deviations/Violations Case Report Form and submitted to the IRB according to their reporting guidelines.

**Consent Process**

Each potential subject must provide written consent with full knowledge of the procedures involved. The informed consent, approved by the IRB and in accordance with regulatory guidelines, must be fully explained by the Investigator or member of the study staff including the study aims, methods, benefits and risks, and signed by the subject before enrollment into the study. Potential subjects will be informed that study participation is voluntary and that they may withdraw at any time. The subjects will be told that choosing against participation will not affect the care received for treatment. The subject will be given sufficient time to read the consent and ask any questions. Once the informed consent is signed, the subject will be given a copy of the document.

**Laws and Regulations**

This clinical study will be conducted in compliance with national laws and regulations, as well as any applicable guidelines. The trial will be registered on UMIN Clinical Trials Registry ([www.umin.ac.jp/ctr/](http://www.umin.ac.jp/ctr/)).

